# A randomized controlled trial of a nurse-led psychological pain solution-focused intervention for depressed inpatients: study protocol

**DOI:** 10.1186/s12912-023-01252-6

**Published:** 2023-04-10

**Keywords:** Psychological pain, Depression, Nursing intervention, Solution-focused brief therapy, Hope theory, Protocol

## Abstract

**Background:**

Depressed patients commonly experience psychological pain. Research pointed to positive psychological interventions as an effective means of ameliorating psychological pain, although the exact effect is unclear. Based on the hope theory and solution-focused brief therapy (SFBT), this study combines hope theory with solution-focused brief therapy to develop a nurse-led psychological pain solution-focused (PPSF) intervention in depressed patients.

**Methods:**

This is an assessor-blinded randomized controlled trial following the SPIRIT guidance. A total of 84 depressed patients will be recruited from the inpatient wards of a psychiatric hospital and randomly assigned to the control and experimental groups. Patients in the control group will be treated as usual. In contrast, patients in the experimental group will receive 6 sessions of the PPSF intervention for two weeks on top of the routine care. Primary outcomes are psychological pain, hope, cognitive distortions. Secondary outcomes are depression and suicidal ideation. Data will be collected at 5-time points: baseline, 1 and 2 weeks (post-intervention), 1 month (follow up), and 6 months after baseline. Generalized equation evaluation will be used to assess the effectiveness of the PPSF intervention.

**Discussion:**

From a positive psychology perspective, there remains much room for developing psychological pain interventions in depressed patients. SFBT and hope theory are both based on positive psychology. With hope theory as the general framework and SFBT questions as the practical guide, the PPSF intervention program is designed that nursing staff can implement. If the intervention is effective, it will advance the development of psychological pain interventions for patients with depression.

**Trial registration:**

ChiCTR2100048223

## Introduction

Depressive disorder is a mental disorder marked by low mood and lack of pleasure that significantly impacts the quality of life. More than 350 million people worldwide are currently estimated to suffer from depressive disorders [1]. In China, the situation is also not optimistic. In the China Mental Health Survey (CMHS), Huang et al. [2] reported the lifetime prevalence of depression in China as 6.9%, exceeding 54 million patients. Depression is the leading cause of suicide, with a rate about ten times higher than that of the general population [3]. As the most common complaint of patients with depression, psychological pain is a risk factor for suicide and plays a central role in suicidal development [4]. Shneidman’s psychache model proposed that “no psychological pain, no suicide”. In other words, when a person’s psychological pain has become unbearable, he will choose suicide to end the pain [5].

As a complex construct, the definition of psychological pain remains inconsistent. Researchers have proposed different definitions of psychological pain from other points of view. Shneidman [5] defined psychological pain in his theory of suicide as an intense, acute mental state accompanied by feelings of guilt, pain, fear, panic, anxiety, loneliness, and helplessness. By applying grounded theory to the emotional pain of individuals with traumatic experiences, Bolger [6] proposed that psychological pain is an individual’s self-awareness of his or her role in the experience of emotional pain, which is fundamentally characterized by a sense of loss or incompleteness of self. Also, Mee et al. [7] defined psychological pain as a diffuse, subjective experience and distinguished it from physical pain produced by physical stimuli that are usually localized. Synthesizing the above perspectives, we attempted to define psychological pain in the domain of depression as a subjective, intensive, and mixed emotional experience that centers on a sense of suffering due to negative self-concept and incompetent coping based on personhood traits [8].

Increasing evidence points to psychological pain as a prominent symptom in depressed patients that aids in assessing and predicting suicide [9, 10]. In the systematic review, Verrocchio et al. [11] found significant positive associations between psychological pain and suicide in the population with depressive disorder. Also, psychological pain plays a mediating role in many variables (e.g., the severity of depressive symptoms, despair, loneliness, adverse life events) and suicide [12–14]. In addition, significant associations were still found when longitudinally assessing the relationship between psychological pain and suicide in patients with psychiatric disorders [15]. This suggests that psychological pain is a stronger predictor of suicide and further emphasizes that early intervention for psychological pain can help prevent and manage suicide. In China, among patients with depressive disorders, the prevalence of psychological pain was 95.78%, which was moderate or higher overall and significantly higher than normal [16, 17]. Given the severity of the situation, it is essential to provide early intervention for psychological pain in depressed patients who may be at risk for suicide but present with psychological pain rather than intervening after it is clear that the suicide risk has emerged.

### Background

In searching and reading the literature on psychological pain interventions in depressed patients, we found many studies of interventions directly targeting suicidal ideation or suicidal behavior in depressed patients. Still, interventions for psychological pain are only in the beginning stages, which may be related to the destructive nature of suicide. Once individuals commit suicide, it causes severe damage to the individual, family, and society, which is much greater than psychological pain. This explains why most of the previous interventions targeted suicide. Only three studies reporting psychological pain interventions for depression patients were searched in the literature. Songprakun and McCann [18] explored the effects of cognitive behavioral bibliotherapy (CBB) in outpatients with moderate depression and measured psychological pain using the Kessler Psychological Distress Scale. Zou et al. [19] used psychological pain theory-based cognitive therapy (PPTBCT) in depressive patients and measured psychological pain using the Three-Dimensional Psychological Pain Scale. Yu [20] used simplified cognitive behavioral therapy(SCBT) for depressed patients with psychological pain, where psychological pain was measured using the Distress Thermometer (DT). These interventions use different types of cognitive behavioral therapy (CBT) and have decreased psychological pain in patients with depression. The focus of these interventions is to guide patients to reduce negative affect, such as CBB’s modification of negative thoughts, PPTBCT’s questioning of irrational beliefs and SCBT’s discovering of negative emotions and dealing with negative beliefs. During the intervention, patients have been in a chronic passive state for a long time, so the experience of positive effects is relatively ignored. However, promoting positive affect is as important a priority in treating depression as reducing negative affect. Positive psychological interventions do not focus on helping patients cure their pathological symptoms but on enhancing positive affect and positive cognition. There is increasing evidence that positive psychological interventions can improve positive emotions and reduce negative emotions [21, 22]. WHO [23] recommends that trained non-professional mental health staff can provide brief psychological treatment to individuals with depression. As those in close contact with depressed patients, nursing staffs are ideal for implementing the intervention. The nurse-led positive psychological intervention can enable patients to discover their potential strengths and capabilities through interventions. Shi et al. [24] stated that nurse-led positive psychological interventions could alleviate depression and improve well-being. Therefore, there is a need to design a brief and practicable nurse-led intervention from a positive psychology perspective to reduce psychological pain.

Solution Focused Brief Therapy(SFBT) [25] is a positive psychology-based, patient-centered, short-term therapy that focuses on the patient’s strengths and the future rather than problems and the past. It is more important to note that SFBT has the advantages of promoting positive affect, short cycle time, low cost, time-effectiveness, and easy operation. We chose SFBT for the intervention based on the following considerations: First, grounded in positive psychology, SFBT adheres to the principle that the patient is the expert in the treatment process, emphasizing the patient’s resources and successful experiences to build solutions to problems jointly. The nature of psychological pain in depressed patients is a negative emotional experience. The key to improving psychological pain is the cognitive reappraisal of emotional events, which means giving new meaning and understanding to emotional events [26]. SFBT can better cope with psychological pain by enhancing positive affect rather than focusing on the causes of psychological pain. Second, SFBT is a highly effective and brief therapy that results in positive changes within 3–4 sessions [27]. It dramatically reduces expenses; on the other hand, it is more acceptable to patients because of the reduced number of sessions. Third, SFBT is a strengths-oriented, patient-centered intervention that fits with the values and principles of nursing. Questioning techniques such as miracle questions and exception questions in SFBT are important ways to drive change in participants, and this is where it is easy to practice. Evidence [28] shows that nurses who complete a brief 2–3-day SFBT training and use SFBT in clinical settings make positive changes to patients and themselves. Also, a qualitative study [29] indicated that SFBT is a beneficial and implementable intervention in the nursing field and that it can be easily integrated by nurses into their clinical work. Therefore, it is reasonable to assume that SFBT is an implementable and brief pathway to reduce the psychological pain of patients with depression that can be implemented by nurses.

### Theoretical framework

Although SFBT offers simple and easy-to-use question techniques, there is no specific and detailed structure for SFBT, and it is challenging to ensure consistency in the implementation of SFBT content. Hope, as one of the four factors of psychological capital, plays an important role in positive psychology [30, 31]. In addition, hope-based intervention has shown positive effects on patient health recovery across broad clinical practices [32–35]. Hope theory was developed by the positive psychologist Snyder and his colleagues [36]. In recent years, it has been gradually applied in the management of mental diseases, which can enable patients to acquire positive thinking ability, so that patients can face the disease in a positive way and reduce their psychological pain [37–40].

Based on the following considerations, we apply the hope theory to guide the study design. First, hope theory and SFBT fall under the umbrella of positive psychology, emphasizing the individual’s strengths and capabilities and focusing on positive emotions such as hope. In principle, Hope theory and SFBT are compatible. Second, compared to SFBT, hope theory provides a more detailed view that guides better design programs. In contrast, SFBT delivers well-used question techniques such as exception questions, scale questions, and miracle questions. In conclusion, integrating SFBT and hope theory is more beneficial in designing programs that reduce psychological pain.

Hope theory includes three components: goal cognition, pathway thinking, and agency thinking, arguing that hope refers to cognition derived from a combination of successful path thinking and agency thinking [41]. Hope theory is more conducive to broadening the depth and breadth of psychological pain research as a framework for understanding pain responses [42]. Furthermore, as emphasized by hope theory, hope is an important psychological resource for individuals to cope with pain and buffer individuals against psychopathology [43]. High-hope individuals are equipped with more positive cognition and are better able to develop strategies to cope with pain and difficulties. Hope as a protective factor can be introduced as a positive motivation at different stages of intervention [44]. Based on Hope Theory and SFBT questions, the intervention strategy in our study was developed around the three components of hope theory of goal cognition, pathway thinking, and agency thinking. And SFBT questions were integrated throughout the intervention as a technical tool. This intervention target is acting on positive cognition, thereby helping to reduce psychological pain, cognitive distortion, depression, and suicidal ideation and improve hope. A conceptual framework is developed, as shown in Fig. 1.

**Fig. 1 Fig1:**
[figure not shown]
Conceptual framework

Therefore, based on the hope theory to provide a general framework and SFBT questions to provide practical guidance, we developed a new intervention program called the Psychological Pain Solution Focused (PPSF) intervention through a literature review of psychological pain intervention studies. If the program is effective, it could be used by nursing staff for interventions for psychological pain in patients with depressive disorders.

## The study

### Aim

This study aims to develop a study protocol for PPSF to improve psychological pain and other psychological variables in patients with depression and to evaluate its effectiveness.

### Hypotheses

Primary hypothesis: compared to the control group, patients in the intervention group receiving the PPSF intervention will have significantly lower psychological pain scores, higher hope scores, and cognitive distortion scores.Secondary hypothesis: compared to the control group, patients in the intervention group will reduce depression scores and suicidal ideation scores after receiving the PPSF intervention.

### Design

The design of this study will be an assessor-blinded, two-arm, randomized, controlled, equivalence trial with an allocation ratio of 1:1. Since psychological interventions are difficult to blind the participants and the researchers conducting the intervention, this study will be blinded only to the researchers assessing the outcome. The protocol will adhere fully to the SPIRIT 2013 statement.

### Study setting

This study will be carried out in a tertiary-A psychiatric hospital in Nanjing, Jiangsu province, which has 16 wards with 573 psychiatric beds. The hospital admits more than 3000 depressed inpatients per year.

### Participants

#### Inclusion criteria

Patients meeting the following criteria will be included: (1) meet the ICD-10 diagnostic criteria for depression; (2) are aged 18–60 years; (3) have depression scores ≥ 20 measured as measured using the 24-item Hamilton Rating Scale for Depression (HAMD-24); (4) have psychological pain scores ≥ 123 as measured using the Orbach & Mikulincer Psychological Pain Scale (OMMP); (5) consent to participate, and (6) can communicate and express themselves with the researchers. We changed the original inclusion criteria from “ ≥ 136” to “ ≥ 123” for OMMP scores because a later cross-sectional study on psychological pain in depressed patients conducted by our team showed that when the OMMP was ≥ 123, it suggested that patients might have suicidal tendencies.

#### Exclusion criteria

Those who have psychiatric co-morbidities, have an intellectual disability, or are undergoing other psychological therapy will be excluded.

### Sample size and recruitment

In this study, the primary outcome of the psychological pain score was selected to calculate the effect sizes. Based on the literature [20], the post-intervention psychological pain score measured using DT was 1.5 ± 0.98 for the experimental group and 2.3 ± 1.05 for the control group, with a statistically significant difference, and an effect size d of 0.788 was calculated. In the G*Power software, the number of participants in each group sample was calculated as 35 cases by using two independent samples t-test and taking bilateral α = 0.05 and 1-β = 0.9. Considering a dropout rate of 20%, the minimum sample size was therefore derived as 84 patients, 42 in each group.

Nurses will introduce the study to depressed inpatients who meet the inclusion criteria, and if a patient agrees verbally to participate, nurses will notify the researchers. The researchers will explain the information about the study in more detail to participants, discuss the appropriate timing of the intervention, and provide informed consent. Then, the participant will return the signed informed consent to the researchers. Participants will be recruited from June 2022 to June 2023, and once recruited, patients will be randomly assigned to the experimental or control group.

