### Data analysis

SPSS 25.0 will be used for statistical analysis of the data. All collected data will be processed for intention-to-treat analysis. ANOVAs and Chi-Square tests were performed to compare demographic and clinical variables, reasons for attrition, and baseline scores on primary and secondary outcomes between the groups, and significant imbalances between the two groups will be checked. Categorical variables will be explored using chi-square tests, and continuous variables will be analyzed using t-tests or Mann–Whitney U tests, thus exploring baseline differences between the two groups. The number of drop-outs and follow-up losses in both groups will be reported based on descriptive data.

This study will compare the differences in primary and secondary outcomes between the two groups at two time points: baseline and 2 weeks(post-intervention). The generalized estimating equation model (GEE) is a statistical model developed based on the generalized linear model, specifically designed to deal with repeated measures such as longitudinal data. Given the association between outcome variables at multiple time points for individuals in our study, the GEE model will be performed to compare the trends of primary and secondary outcomes at different time points (baseline, 1 week, 2 weeks, 1 month, and 6 months) in the two groups, adjusted for confounding factors of statistical differences in the baseline. The GEE model will be applied to explore the effects of time factors, intervention factors, and interactions between intervention factors and time factors on each variable between the two groups. When there is an interaction effect, then the analysis of the simple effects will be adopted. In this study, no subgroup analysis will be performed. To reduce the risk of type I errors, Bonferroni correction will be used for multiple comparisons, that is, dividing 0.05 by the number of comparisons. Thus, *P* < 0.01 represents a statistically significant difference.

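### The trial is sized at two-sided 0.05 but declares significance only at P < 0.01, so the stated 90% power is about 72–74% under the protocol's own t-test

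*Protocol article*

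**What the plan says.** The protocol article, under Sample size and recruitment, sizes the trial on the psychological pain score. The cited post-intervention score "was 1.5 ± 0.98 for the experimental group and 2.3 ± 1.05 for the control group", from which "an effect size d of 0.788 was calculated". On the group size it says that "the number of participants in each group sample was calculated as 35 cases by using two independent samples t-test and taking bilateral" alpha of 0.05, with power of 0.9; the settings read in full "taking bilateral α = 0.05 and 1-β = 0.9". The allowance for loss follows: "Considering a dropout rate of 20%, the minimum sample size was therefore derived as 84 patients, 42 in each group".

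Under Data analysis, the article plans a between-group comparison at baseline and 2 weeks and a GEE model over all five time points. It says Bonferroni correction will be used, with 0.05 divided by the number of comparisons, and closes with the rule that P < "0.01 represents a statistically significant difference". It does not list the comparisons being counted, and it does not say that psychological pain is tested at any other level. The Abstract names three primary outcomes: psychological pain, hope and cognitive distortions.

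**The concern.** Power belongs to a particular test at a particular threshold. The article claims 90% power at 0.05 and then sets 0.01 as the level at which a result counts. Both figures are stated, so this is not a detail left to a fuller document.

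Two things are at stake. First, the stated 10% risk of missing the planned effect is too low for the declared rule. Second, a P value between 0.01 and 0.05 for psychological pain would meet the level used for sizing and fail the level used for analysis. Unless the article settles which one applies, the choice could be made after the data are seen.

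**Working it through.** **Inputs, all from the protocol article**

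- Means 1.5 and 2.3, SDs 0.98 and 1.05, two-sided alpha 0.05, power 0.90, two-sample t-test, 20% dropout, 42 per group (Sample size and recruitment).
- Design "with an allocation ratio of 1:1" (Design).
- Significance at P < 0.01 (Data analysis).

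**Step 1: effect size**

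Pooled SD = √((0.98² + 1.05²)/2) = √((0.9604 + 1.1025)/2) = 1.0156. Then d = (2.3 − 1.5)/1.0156 = 0.788, which agrees with the article.

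**Step 2: the article's own sample size**

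For n analysed per group, the t statistic has df = 2n − 2 and noncentrality d√(n/2). Power is the probability, under that noncentral t distribution, of exceeding the two-sided critical value.

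With n = 35, df = 68, noncentrality = 0.788 × √17.5 = 3.296 and the critical value at 0.05 is 1.995. Power is 90.1%. The figure of 35 per group reproduces, so the method and inputs are the article's own.

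**Step 3: change only the threshold to 0.01**

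With n = 35 the noncentrality stays at 3.296, but the critical value rises to 2.650. Power falls to 73.9%.

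**Step 4: allow for different numbers analysed**

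The article reaches 42 as 35 × 1.2. A loss of 20% from 42 leaves 42 × 0.8 = 33.6, slightly below 35.

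| Analysed per group | Power at 0.05 | Power at 0.01 | Chance of missing the effect at 0.01 |
|---|---|---|---|
| 33.6 (42 less 20%) | 88.9% | 71.6% | 28.4% |
| 35 (the article's target) | 90.1% | 73.9% | 26.1% |
| 42 (no dropout) | 94.6% | 83.2% | 16.8% |

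**Step 5: what 90% power at 0.01 would take**

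It needs 50 analysed per group (49 gives 89.6%, 50 gives 90.3%). Alternatively, with 35 per group, d would have to be about 0.95 instead of 0.788. Fifty analysed per group means 50/0.8 = 62.5, so 63 recruited per group and 126 in total, against the planned 84.

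**Step 6: sensitivity to the correction**

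A threshold of 0.01 implies 0.05/0.01 = 5 comparisons. Five outcomes or five time points would both fit. If the correction covered only the three primary outcomes, the level would be 0.05/3 = 0.0167, and power with 35 per group would be 79.7%.

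**The case against.** **Less dropout by week 2.** The powered comparison is post-intervention, at 2 weeks. The article says stays are commonly 2–3 weeks and that the first three measurements are made on the ward. Loss by then may be well under 20%, and the analysis is by intention to treat. With 40 analysed per group, power at 0.01 is 80.9%; with all 42 it is 83.2%. This stands as a reason to show the upper figure, but it does not restore 90%. The 90% claim was itself made for 35 analysed.

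**GEE is not a t-test.** The longitudinal analysis includes baseline and a group-by-time interaction, so its power depends on the correlation between baseline and week 2. The article does not give that correlation. As an assumption, take a change-from-baseline contrast with 35 per group at 0.01: power is 55.7% at a correlation of 0.3, 73.9% at 0.5, 84.6% at 0.6 and 94.2% at 0.7. The power of the GEE could therefore lie on either side of the figure here. This limits the finding to the test on which the article bases its power claim. It does not support that claim, which makes no use of a correlation.

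**Scope of the 0.01 rule.** The sentence comes after the simple-effects step and speaks of multiple comparisons, so it could be meant for follow-up contrasts only. That reading is possible but less natural, because the rule is unqualified and closes the whole analysis section. If the narrower meaning is intended, the article has to say so.

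**Direction of the error.** A stricter threshold does not inflate the type I error. That is true; the harm is an overstated power figure and an unsettled decision rule.

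**Conclusion.** The concern holds. At the article's effect size and with its own t-test, power at the declared threshold is 73.9% with 35 analysed per group and 71.6% after a 20% loss from 42. The risk of missing the planned effect is about 26–28%, more than two and a half times the 10% implied. With no dropout at all, power is 83.2%.

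This rests on three assumptions: that P < 0.01 governs psychological pain, as the general wording indicates; that d = 0.788 is the effect of interest; and that the deciding comparison is the two-sample t-test used for sizing. The power of the GEE cannot be computed from the article.

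**What to change.** Make the threshold and the power statement agree, and record the choice with a date before any between-group outcome data are examined. There are two ways.

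1. **Keep P < 0.01.** In Data analysis, list the five comparisons that give 0.01 and say whether the 2-week comparison of psychological pain is among them. If it is, restate power in Sample size and recruitment as about 74% with 35 analysed per group and 72% after 20% dropout. The cost is wording and a less favourable power figure; the hypotheses do not change.

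2. **Use the alpha the trial was sized on.** Name the OMMP score at 2 weeks as the first and only powered comparison, tested at two-sided 0.05. Test the remaining outcomes after it in a stated fixed order, and delete the P < 0.01 rule. This keeps the 90% claim for 35 analysed and controls the overall type I error across that sequence. It costs more than wording: hope and cognitive distortion would become conditional on psychological pain, which alters the primary hypothesis, and the order must be set after recruitment has begun (it was scheduled from June 2022).

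The first is the smaller change. The second is preferable if the investigators want the powered comparison to decide the trial and accept the hierarchy. Neither needs extra patients. Holding both 0.01 and 90% power would need about 126.

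### The planned 84 patients do not leave the required 35 per group after 20% dropout; they cover a dropout of 16.7%

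*Protocol article*

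**What the plan says.** The sample size is set in the protocol article under Sample size and recruitment, on the psychological pain score. The inputs come from a cited study that used the Distress Thermometer, where the post-intervention score "was 1.5 ± 0.98 for the experimental group and 2.3 ± 1.05 for the control group". From these, "an effect size d of 0.788 was calculated". The number per group was found in G*Power "by using two independent samples t-test" and "taking bilateral α = 0.05 and 1-β = 0.9", with the result that "the number of participants in each group sample was calculated as 35 cases".

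The dropout allowance follows in one sentence: "Considering a dropout rate of 20%, the minimum sample size was therefore derived as 84 patients, 42 in each group". No inflation formula is given. The Design section fixes 1:1 allocation. No other section revisits the number.

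**The concern.** A dropout rate is a share of the patients enrolled. An allowance for 20% dropout should therefore leave the required number once a fifth of those enrolled are gone. Here it does not: a fifth of 42 is 8.4, and 33.6 is fewer than 35. Yet the sentence presents 84 as the smallest enrolment that meets the requirement at 20% dropout.

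Three printed figures are at stake: enrolment, dropout rate and power. Taken with the required 35 per group, they cannot all hold. If dropout reaches the planned level, the trial falls below its own required number. That level is realistic. The Limitations section itself expects that the intensity of the sessions and the 6-month follow-up may cost patients, and Data collection places the last two assessments in the outpatient clinic.

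**Working it through.** **Inputs**, all from Sample size and recruitment: means 1.5 and 2.3; SDs 0.98 and 1.05; two-sample t-test; two-sided alpha 0.05; power 0.90; dropout 20%; 42 per group, 84 in total.

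**Step 1: effect size.** The pooled SD is √((0.98² + 1.05²)/2) = √((0.9604 + 1.1025)/2) = 1.0156. Then d = (2.3 − 1.5)/1.0156 = 0.7877, which agrees with the printed 0.788.

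**Step 2: number per group before dropout.** By the exact noncentral t calculation at d = 0.788 and two-sided 0.05, power is 0.893 with 34 per group and 0.901 with 35. The smallest number that reaches 0.90 is 35, as the protocol says. The base calculation is sound.

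**Step 3: dropout allowance.**

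| Method | Per group | Total |
|---|---|---|
| 35 × (1 + 0.20) | 42 | 84 |
| 35 / (1 − 0.20) | 43.75, rounded up to 44 | 88 |

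The first line reproduces the protocol's figure exactly; the second is what a 20% loss requires. As a check, 44 × 0.80 = 35.2, which meets 35, while 43 × 0.80 = 34.4 does not. The gap is 88 − 84 = 4 patients, or 4/84 = 4.8% of the planned total.

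Rounding in the base figure does not explain the result. A normal approximation gives 34 per group, and 34 × 1.2 = 40.8 (41) or 34/0.8 = 42.5 (43). Neither is 42.

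**Step 4: what 84 delivers.**
- At 20% dropout: 42 × 0.80 = 33.6 per group, and 84 × 0.80 = 67.2 in total, against a requirement of 35 and 70.
- Dropout that still leaves 35 per group: 1 − 35/42 = 7/42 = 16.7%.

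**Step 5: power at d = 0.788, two-sided 0.05, noncentral t.**

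| Evaluable per group | Power |
|---|---|
| 33 | 88.3% |
| 33.6 | 88.9% |
| 34 | 89.3% |
| 35 | 90.1% |

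The cost of the error is 90.1 − 88.9 = 1.2 percentage points.

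**Step 6: the 0.01 threshold.** The Data analysis section declares significance at P < 0.01. At that level, power is 73.9% with 35 per group and 71.6% with 33.6. The dropout step accounts for 73.9 − 71.6 = 2.3 points. The rest of the fall from 90% comes from powering at 0.05 and testing at 0.01, which is a separate matter.

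**The case against.** The arithmetic is not in dispute; the weight of the point is. Four arguments deserve an answer.

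- **The loss is tiny.** Power falls by 1.2 points, and 0.889 rounds to the 0.9 that the protocol prints. This is true, and it keeps the point modest. It does not rescue the sentence, which claims a minimum enrolment for 20% dropout and misses the stated 35 per group.
- **The 20% is not tied to a time point.** The calculation uses the post-intervention score, and the 2-week assessment is planned in the ward, where losses may be lower than at 6 months. If loss by 2 weeks is 16.7% or less, 35 per group remain. The planned intention-to-treat GEE over five time points can also use earlier data from patients lost later. Both are fair, but they are reasons to expect less than 20% loss at the powered time point. They do not make 84 the right number for 20%.
- **Chance imbalance matters more.** Under simple randomization, if 84 patients are each allocated independently, the size of one arm has a standard deviation of √84/2 ≈ 4.6, so 42 and 42 are nominal. This is correct, and it also means there is no spare margin to absorb a shortfall.
- **The multiplication by 1.2 is inferred.** No formula is printed. The exact match makes it very likely, but the conclusion needs only the fact that 42 less 20% is below 35.

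**Conclusion.** The concern holds. The effect size and the 35 per group are right. The dropout step is wrong as written: 84 patients cover 16.7% dropout, not 20%, and the total that would cover 20% is 88.

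The consequence is small. At the protocol's own dropout rate, power is about 89% (88.3% with 33 per group, 89.3% with 34) instead of 90%. These figures rest on the protocol's d = 0.788, its t-test at two-sided 0.05, equal groups, and a 20% loss at the time point on which the trial is powered. The statement should be corrected, but the error does not threaten the trial.

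**What to change.** Keep 84 patients and rewrite the sentence on dropout in Sample size and recruitment. Either of these is accurate:

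- *84 patients (42 per group) allow for 16.7% dropout at 90% power, two-sided alpha 0.05.*
- *With 84 patients and 20% dropout, 33 to 34 per group remain, giving about 89% power at two-sided alpha 0.05.*

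The second leaves the dropout assumption as it is. Enrolling 88 (44 per group) would also reconcile the figures, but 4 more patients for about one point of power is not needed.

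The cost is one sentence and a slightly less favourable stated figure. No patients are added, and neither the design nor the analysis changes.
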